## 2.2 Hypothesis

Previous studies have demonstrated that a 3 week interval between homologous MVA85A–MVA85A administered systemically does not enhance responses (8). We hypothesise that responses will be boosted in the aerosol–systemic and systemic-aerosol group but not in the systemic–systemic group.

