#### **\* Change to Group 2 vaccinations**

A change has been made for group 2 volunteers due to receive their day 28 boost vaccination on or after 2 September 2015, due to a higher frequency of mild respiratory adverse events in this group. Local (skin) and systemic symptoms were as expected and consistent with data from previous studies. These volunteers will not receive the day 28 boost vaccination, but instead will receive a placebo by both intradermal and aerosol inhaled routes to maintain blinding. Additional safety and immunological information will be gained by continuing with day 35 bronchoscopy in these volunteers. Any volunteer not wishing to proceed in this manner will remain in follow up with no vaccination or bronchoscopy.

As BCG is protective in childhood, it is routinely given at birth in TB endemic countries but is also in widespread use in children and adolescents in much of the rest of the world. Therefore, as in previous trials of intradermal MVA85A, we propose to vaccinate BCG-primed subjects. These will be healthy men and women aged 18-55 years who have been previously vaccinated with BCG.

All subjects will have received BCG vaccination at least six months prior to enrolment. MVA85A ( $5 \times 10^7$  pfu) or saline placebo will be administered by systemic (intradermal) or aerosol (Omron jet nebuliser) route (paired placebo design). The interval between the two vaccinations is one month.

In order to minimise the risk from bronchoscopy, subjects with a history or evidence of lung disease will be excluded. This will be determined by our standard screening procedures (history, examination, urine analysis, and blood tests), and, in addition, a chest x ray and pulmonary function testing.

The peak effector T-cell response in blood is ~7 days post-vaccination with MVA85A. Pulmonary mucosal responses are expected to follow a similar time course and a preclinical study has demonstrated this in non-human primates (35). Thus bronchoscopy and bronchialveolar lavage will be performed seven days after each vaccination.

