# **9. STATISTICS**

## **9.1 Statistics**

This is primarily a trial with descriptive endpoints. Twelve subjects will be recruited into each arm of the trial (i.e. 36 in total). Our previous experience with clinical trials using MVA85A over the last 10 years suggests that this sample size is a feasible number to recruit, screen, enroll, and follow up in practical terms, whilst also allowing the determination of any substantial and clinically significant differences in safety and cell-mediated immunity between the three groups. A twofold increase in the magnitude of the cellular immune response (as measured by Elispot response to 85A peptide stimulation) is considered immunologically meaningful. Extrapolating effect size and variability from the completed initial aerosol vaccine safety study (TB026), twelve volunteers are needed to have 80% power to detect an immunologically meaningful difference in the summed peptide pools and 8

volunteers to achieve the same for single peptide pool of 85A. This sample size is appropriate for a proof-of-concept Phase I safety study.

It is anticipated that the immunological endpoints will not follow a normal distribution. A log transformation will be applied and if the resulting data are normally distributed they will be summarised by group using means and standard deviations. The one-week and six-month responses will be compared between the three groups using a t-test. If the resulting data are not normally distributed then medians and interquartile ranges will be used to summarise the data and the Mann Whitney U test will be used for statistical comparisons. An area-under-curve analysis will be used to compare the overall responses over time between the three groups. This analysis will make use of data collected at all time points.

Differences between means or medians between the three groups will be presented along with their 95% confidence intervals. Within each group, paired data will be analysed using either a paired t-test or the Wilcoxon matched pairs test depending on the normality of the data.

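### Section 9.1 was not updated for the v4.0 change to Group 2, so its analyses using data after day 28 still treat boosted and unboosted volunteers as one systemic-aerosol arm

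*Protocol*

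**What the plan says.** Section 4.1 (Change to Group 2 vaccinations) states for Group 2 volunteers whose boost falls due from 2 September 2015: "These volunteers will not receive the day 28 boost vaccination, but instead will receive a placebo by both intradermal and aerosol inhaled routes". It adds: "Any volunteer not wishing to proceed in this manner will remain in follow up with no vaccination or bronchoscopy". The trial regimen in Section 6.1 lists both day 28 options for Group 2, aerosol MVA85A or saline by both routes. Group 2 can therefore hold up to three kinds of volunteer after day 28.

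Section 2.2 still states: "We hypothesise that responses will be boosted in the aerosol–systemic and systemic-aerosol group but not in the systemic–systemic group".

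Section 9.1 still plans on: "Twelve subjects will be recruited into each arm of the trial (i.e. 36 in total". It compares the three groups at one week and six months by t-test or Mann-Whitney test and adds an AUC: "An area-under-curve analysis will be used to compare the overall responses over time between the three groups". The AUC is to use every time point. Within each group, paired data are tested by paired t-test or Wilcoxon test. Nothing in 9.1 says how volunteers who did not get the aerosol boost are handled.

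**The concern.** The second secondary objective asks whether anti-vector immunity matters functionally, and it is judged by what the boost does. For the systemic-aerosol regimen, only volunteers who received the aerosol boost can answer that. Section 9.1 names a group, not a dose received, so the stated analysis averages boosted and unboosted volunteers and reports the result under the systemic-aerosol label. The weights in that average are set by when each volunteer reached day 28 and, for any who declined, by their own choice. Neither is randomised.

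The affected analyses are the six-month comparison, the part of the AUC after day 28, and any paired test in Group 2 that uses later data. A paired test across the boost is the most direct check of Section 2.2. If the one-week comparison is also meant one week after the boost (day 35), it is affected too. Data up to the day 28 dose, including day 7, are not affected, because every Group 2 volunteer had the same intradermal prime.

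**Working it through.** **Inputs from Section 9.1.** Twelve per arm. The meaningful effect is twofold ("A twofold increase in the magnitude of the cellular immune response"), which is log10(2) = 0.3010. The stated power is: "twelve volunteers are needed to have 80% power to detect an immunologically meaningful difference in the summed peptide pools". The variability is drawn from an earlier trial without a figure: "Extrapolating effect size and variability from the completed initial aerosol vaccine safety study (TB026").

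**Not in the document.** The SD, the significance level, the type of comparison and the number of Group 2 volunteers switched.

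**The plan's own figure.** Without an SD, the twelve can be neither reproduced nor refuted. Solving backwards for 80% power at 12 v 12 with an unpaired two-sided 5% t-test (noncentral t) gives a standardised difference of 1.197, so SD = 0.3010 / 1.197 = 0.252 on the log10 scale. The normal approximation gives 0.263. A paired reading would give 0.339 for the within-person difference. I use 0.252 as an assumption.

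**Effect of pooling on one post-boost outcome.** Let u of the 12 be unboosted, with a true twofold effect in the rest.

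- Expected log10 difference from an unboosted comparator = 0.3010 × (12 − u) / 12.
- Apparent ratio = 2^((12 − u)/12). For u = 6 this is 2^0.5 = 1.41.
- Pooled power is from a simulated t-test of 12 v 12. Boosted-only power is the noncentral-t power of (12 − u) v 12.

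| Unboosted of 12 | Apparent ratio, pooled | Power, pooled | Power, boosted only (expected ratio 2.0) |
|---|---|---|---|
| 0 | 2.00 | 80% | 80% |
| 1 | 1.89 | 71% | 78% |
| 2 | 1.78 | 61% | 76% |
| 3 | 1.68 | 50% | 73% |
| 6 | 1.41 | 23% | 61% |
| 9 | 1.19 | 8% | 40% |

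The expected ratio of 2.0 for boosted volunteers holds only if those enrolled before and after the switch are otherwise alike.

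**Direction depends on the contrast.** Against Group 3, which Section 2.2 expects not to be boosted, pooling pulls the ratio towards 1. Against Group 1, which Section 2.2 expects to be boosted, it does the opposite. If Groups 1 and 2 would respond equally when boosted, the pooled arm falls short by a factor of 2^(u/12): 1.06, 1.19, 1.41 or 1.68 for u = 1, 3, 6 or 9.

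**The AUC.** These ratios do not carry over to the AUC, which also contains unaffected data up to day 28. On the time axis 168 − 28 = 140 of 168 days lie after the boost. The dilution depends on the shape of the response curve, which the document does not give.

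**The case against.** Section 9.1 does not order pooling; it is silent on the switch. Section 6.1 already separates the two Group 2 regimens, and a statistical analysis plan that is not shown may define subsets by dose received. The endpoints are called mainly descriptive. The number switched may be small: with one or two unboosted, pooled power is still 71% or 61%. No opt-out is documented.

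Much of this stands, and it limits the severity. It does not remove the point. The protocol does not leave the comparison open: it fixes a three-group comparison over all time points, and those groups no longer match its regimens. A descriptive mean or AUC under the wrong regimen label is still mislabelled. Nor is pooling simply intention-to-treat, because apart from opt-outs the protocol itself assigned different day 28 regimens by date.

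Three stronger readings are tempting, and the documents do not support them.

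- A reader might infer that aerosol-boost adverse event rates are diluted too. Section 9.1 mentions safety differences between groups only when justifying the sample size and sets no Group 2 adverse event summary. Section 3 ties the primary endpoint to inhaled MVA85A, so volunteers given saline on day 28 are not in that denominator.
- A reader might call the Group 2 result uninterpretable. That fails where few were switched, and the data remain usable when split by dose received.
- A reader might take the boosted-only comparison as unbiased. That subset is selected by calendar date.

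**Conclusion.** The point holds: Sections 9.1 and 2.2 were not brought into line with the v4.0 regimen. After day 28 the pooled Group 2 result does not estimate the systemic-aerosol regimen. The loss ranges from slight (one unboosted) to near-complete (nine unboosted), and the document does not allow it to be narrowed. Dilution presumes that the aerosol boost has an effect; the mislabelling does not depend on that. All power figures rest on the back-solved SD, a twofold effect, an unpaired two-sided 5% test and a single post-boost outcome. Separating the subsets costs sample size but, under these assumptions, has more power than pooling at every number of unboosted volunteers tabulated. Severity: should be fixed. It concerns secondary immunological endpoints with an unknown number affected, and no view is taken on the dosing change itself.

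**What to change.** Amend Section 9.1, and align Section 2.2 with it:

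- Up to the day 28 dose, keep all Group 2 volunteers together as intradermally primed.
- After it, analyse and report Group 2 by day 28 dose received (aerosol MVA85A, saline, none), give the n of each, and do not pool them. Apply this to the six-month comparison, the AUC, paired tests and any day 35 comparison.
- Let only the aerosol-boosted subset carry the systemic-aerosol hypothesis.
- State that this subset is selected by calendar date, so its comparison with Groups 1 and 3 is no longer fully randomised. Add a sensitivity comparison limited to volunteers enrolled over the same period.
- Allow the saline subset as a non-randomised intradermal-prime-only reference for Group 3. It cannot serve Group 1, whose prime is aerosol.
- State that 12 per arm and 80% power no longer apply to systemic-aerosol comparisons after day 28.

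The cost is wording in the protocol or the analysis plan, and a smaller systemic-aerosol set with wider intervals. No dose, visit or procedure changes.

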## 3. OBJECTIVES AND OUTCOME MEASURES/ ENDPOINTS

| Objectives                                                                                                                                                                                                                                                                                                                                                                                                       | Outcome Measures/Endpoints                                                                                                                                                                                                                                                                                                                                                                          |
|------------------------------------------------------------------------------------------------------------------------------------------------------------------------------------------------------------------------------------------------------------------------------------------------------------------------------------------------------------------------------------------------------------------|-----------------------------------------------------------------------------------------------------------------------------------------------------------------------------------------------------------------------------------------------------------------------------------------------------------------------------------------------------------------------------------------------------|
| Primary Objective
To evaluate the safety of $5 \times 10^7$ pfu dose of MVA85A administered by aerosol and compared to the same dose administered intradermally.                                                                                                                                                                                                                                       | Safety of $5 \times 10^7$ pfu dose MVA85A administered by the inhaled route through actively and passively collected data on adverse events.                                                                                                                                                                                                                                                        |

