### **Trial regimen**

Group 1: Aerosol inhaled MVA85A  $5 \times 10^7$  pfu (and intradermal saline placebo) on day 0, followed by homologous boosting with MVA85A  $5 \times 10^7$  pfu intradermal on day 28 (and aerosol inhaled saline placebo)

Group 2: Intradermal MVA85A  $5 \times 10^7$  pfu (and aerosol inhaled saline placebo) on day 0, followed by homologous boosting with MVA85A  $5 \times 10^7$  pfu aerosol inhaled on day 28 (and intradermal saline placebo) OR, following safety amendment (see section 4.1)

Intradermal MVA85A  $5 \times 10^7$  pfu (and aerosol inhaled saline placebo) on day 0, followed by aerosol inhaled saline placebo and intradermal saline placebo on day 28

Group3: Intradermal MVA85A  $5 \times 10^7$  pfu (and aerosol inhaled saline placebo) on day 0, followed by homologous boosting with MVA85A  $5 \times 10^7$  pfu intradermal on day 28 (and aerosol inhaled saline placebo)

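### Groups 2 and 3 are treated identically until day 28, but section 9.1 never pools them, so first-dose route contrasts are valid but less precise than they could be

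*Protocol*

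**What the plan says.** The primary objective (section 3) is a contrast of two routes: safety of the dose "administered by aerosol and compared to the same dose administered intradermally".

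Section 9.1 works with three regimens. The sample size is justified as "allowing the determination of any substantial and clinically significant differences in safety and cell-mediated immunity between the three groups". One-week and six-month immune responses are compared between the three groups with a t-test or Mann-Whitney test, area under the curve is compared between the three groups, and "Differences between means or medians between the three groups will be presented along with their 95% confidence intervals". The section does not mention combining groups or a contrast by route.

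Under Trial regimen in section 6.1, the rows for Groups 2 and 3 describe the same first dose: intradermal MVA85A "and aerosol inhaled saline placebo) on day 0, followed by homologous boosting with MVA85A". Table 3 (section 4.1) gives both groups a bronchoscopy one week later. They part only at day 28. The later change to Group 2 (section 4.1) replaces the day 28 aerosol boost with placebo by both routes for volunteers whose boost was due on or after 2 September 2015. It leaves the first dose unchanged.

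**The concern.** Two issues follow, one before the boost and one after it.

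Before day 28 the design randomises 12 volunteers to aerosol and 24 to intradermal vaccine. Three pairwise comparisons at day 7 then include one (Group 2 v 3) that can differ only by chance. The other two ask the same question twice, each with half of the available comparator. The two answers may disagree, and section 9.1 gives no rule for reading them together.

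Over the whole follow-up, an adverse event total per group does not correspond to a route. Group 1 and unamended Group 2 each receive both routes, in opposite order. Amended Group 2 receives active vaccine intradermally only, and Group 3 intradermally twice. A table with one column per group would not answer the primary objective directly. It would also make the respiratory events that led to the Group 2 change harder to read.

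**Working it through.** **Inputs**
- Arm size: "Twelve subjects will be recruited into each arm of the trial (i.e. 36 in total".
- Power statement: "twelve volunteers are needed to have 80% power to detect an immunologically meaningful difference in the summed peptide pools".
- Effect: "A twofold increase in the magnitude of the cellular immune response (as measured by Elispot response to 85A peptide stimulation) is considered immunologically meaningful". On the log10 scale, log10(2) = 0.301.
- SD: not given; the protocol says only "Extrapolating effect size and variability from the completed initial aerosol vaccine safety study (TB026".
- Alpha, sidedness and type of test behind the 12: not given. Two-sided 0.05 is assumed, in line with the 95% intervals.

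**Step 1. The protocol's own figure.** The 12 cannot be reproduced without an SD, so the SD is solved from it. For a two-sample t-test, 12 v 12, 80% power at a difference of 0.301, the log10 SD is 0.252 (standardised effect 0.301/0.252, about 1.20). A normal approximation gives 0.263. Read as a paired test, the 12 would imply an SD of differences of 0.339 and would say nothing direct about a contrast between groups.

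**Step 2. Variance of the route contrast** (in units of the SD squared)
- One intradermal group: 1/12 + 1/12 = 0.1667
- Groups 2+3: 1/12 + 1/24 = 0.1250
- Ratio 0.1250/0.1667 = 0.75, so the unpooled variance is 1/0.75 = 1.33 times the pooled one.
- SE ratio √0.75 = 0.866, a fall of 13.4%.

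**Step 3. Power for a twofold difference** (noncentral t, SD 0.252)
- 12 v 12: SE = 0.252 × √0.1667 = 0.103; noncentrality 0.301/0.103 = 2.93 on 22 df; power 80.0%
- 12 v 24: SE = 0.252 × √0.125 = 0.089; noncentrality 0.301/0.089 = 3.39 on 34 df; power 90.8%
- Ratio detectable with 80% power: 2.0 and 1.80 respectively
- Normal approximation at SD 0.263: 80.0% and 89.9%

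**Step 4. Range of SD.** As the SD is unstated:

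| Assumed log10 SD | 12 v 12 | 12 v 24 |
|---|---|---|
| 0.20 | 94.1% | 98.5% |
| 0.30 | 65.2% | 78.7% |
| 0.40 | 42.2% | 54.3% |
| 0.50 | 29.1% | 38.0% |

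**Step 5. Two separate route tests.** In a simulation with a true twofold effect and SD 0.252, Group 1 v 2 and Group 1 v 3 are both significant in about 69% of trials. Exactly one is significant in about 23%.

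**Step 6. Adverse events, illustration only.** The protocol names no safety test and gives no design event rates. With Fisher's exact test at two-sided 0.05, power for 60% v 20% goes from 39% to 56%, and for 70% v 20% from 61% to 77%. The gain depends on the comparator rate. If half of intradermal recipients have the event, 12 v 24 still needs an aerosol rate of about 95% for 80% power.

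**The case against.** A reader might infer that the plan wastes a third of the data. It does not: all 36 volunteers enter the set of comparisons. Each single route contrast leaves out 12 of them, and the price is the 33% in variance, or 13% in SE, shown above.

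A reader might also infer that the plan cannot isolate route. Up to day 28 that is wrong. Group 1 v 2 and Group 1 v 3 are randomised, paired-placebo contrasts that differ only in route. They are inefficient, not confounded.

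On safety, section 9.1 calls the endpoints primarily descriptive, and the three groups are mentioned for safety only in the sample size rationale. No three-group safety test is fixed, and table layout may sit in a statistical analysis plan that is not at hand. Nor is it true that events cannot be tied to a route. Section 8.3 records start and stop dates and 14-day diary cards, Table 4 lists local events separately for each route, and section 8.2 grades causality. Attribution per dose is possible; section 9.1 just does not ask for it.

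The one-week response is not tied to a day. If it means day 35, one week after the boost, three groups are right, because the hypothesis in section 2.2 concerns boosting in three regimens. The null-by-construction point applies only to day 7.

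Pooling also has a cost. Section 4.3 describes a separate restart of Group 2 enrolment, so some of its volunteers may not be concurrent with Groups 1 and 3. And if the first-dose contrast stood alone for safety, it would leave out every Group 2 aerosol boost.

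All of these points stand. They reduce the concern to one of precision and clarity but do not remove it. The comparison that section 9.1 does state is by regimen, while the primary objective is by route.

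**Conclusion.** The point holds as a cheap improvement, not as a flaw that invalidates the analysis. That Groups 2 and 3 are identical until day 28, and that section 9.1 neither pools them nor names a contrast by route, rests on the text alone. So does the mixing of routes in full-follow-up totals per group.

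The variance ratio of 0.75 and the 13% fall in SE need only 12 and 24 evaluable volunteers with a common SD. The rise in power from 80% to about 91%, and the fall in detectable ratio from 2.0 to 1.80, also assume a two-sample t-test, two-sided alpha 0.05 and the back-solved SD of 0.252. The gain is in the same direction over the whole assumed range, from 94% to 98.5% at SD 0.20 and from 29% to 38% at SD 0.50. The adverse event figures are illustrations and should not be quoted as properties of this trial.

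**What to change.** In section 9.1:
1. For safety and immune outcomes before the day 28 dose, compare Group 1 (aerosol, 12) with Groups 2 and 3 combined (intradermal, 24), with a 95% confidence interval. Drop Group 2 v 3 as a treatment comparison at these times.
2. State whether the one-week response is day 7, day 35 or both. The pooled contrast applies to day 7 only.
3. Keep the three-regimen comparison after day 28, with Group 2 volunteers who received placebo at day 28 shown separately.
4. Tabulate adverse events per dose by route received, and after dose 2 also by the preceding route. Events after the Group 2 aerosol boost then stay visible beside the first-dose contrast.
5. Show the pooled contrast with and without Group 2 volunteers enrolled after the restart. Without them the comparator lies between 12 and 24, and the gain is smaller accordingly.

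The cost is a change of wording and one sensitivity analysis, with no new volunteers, visits or samples.

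### Section 9.1 pairs the Mann-Whitney test with a difference between medians, which that test does not assess, and leaves open the scale on which the difference is reported

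*Protocol*

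**What the plan says.** Protocol section 9.1 sets out one route for the immunological endpoints. Values are log-transformed. If the result looks normal, groups are summarised by means and SDs and compared by t-test. If not, they are summarised by medians and interquartile ranges, and "the Mann Whitney U test will be used for statistical comparisons". One sentence then defines the reported effect for both branches: "Differences between means or medians between the three groups will be presented along with their 95% confidence intervals". Within-group comparisons use a paired t-test or the Wilcoxon matched-pairs test.

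The same section gives the only yardstick for effect size: "A twofold increase in the magnitude of the cellular immune response (as measured by Elispot response to 85A peptide stimulation) is considered immunologically meaningful". The sample size rests on it: "twelve volunteers are needed to have 80% power to detect an immunologically meaningful difference in the summed peptide pools", with variability taken from TB026 but not stated.

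The section does not name the method for the median interval. It does not say whether medians in the non-normal branch are on log or raw values, and it does not mention ratios.

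**The concern.** Mann-Whitney works on the ordering of all pairs of values, one from each group. Under a pure shift model, the estimate that belongs to it is the median of all pairwise differences (the Hodges-Lehmann shift). That is a different statistic from the difference between the two sample medians, and with 12 per arm the latter is noisier. Read literally, the plan can print p < 0.05 beside an interval that contains zero, or the reverse.

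The scale is a second gap. Ranks do not change under a log transformation, so the Mann-Whitney p-value is the same on either scale and does not settle which one the reported difference uses. The meaningful effect is a ratio. A difference of log medians back-transforms to a ratio, but a difference of raw medians does not.

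These comparisons serve the secondary objectives in section 3 and the boosting hypothesis in section 2.2. In a largely descriptive trial, estimates and intervals are the main product of such comparisons.

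**Working it through.** **Inputs from section 9.1:** 12 per arm, a twofold effect (ln 2 = 0.693) and 80% power. **Assumed:** two-sided 5% (consistent with the 95% intervals), the log-scale SD, the distribution shapes and the interval methods.

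**1. The plan's own figure.** The stated n cannot be reproduced because no SD is given. It can be inverted. From n = 2(1.96 + 0.842)² SD² / (ln 2)², n = 12 per arm gives SD = 0.693 × √(12 / 15.70) = 0.61 on the natural-log scale (0.58 by the noncentral t). The single-pool figure of 8 gives 0.693 × √(8 / 15.70) = 0.49 (0.46 by t). If 12 meant a paired comparison, the SD of differences would be 0.693 × √(12 / 7.85) = 0.86. A log SD of 0.60 is therefore a reasonable setting for two arms of 12.

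**2. Test against interval.** 12 v 12, 3,000 runs per scenario, four shapes on the log scale (normal, heavy-tailed, bimodal, skewed). Disagreement means that exact Mann-Whitney p < 0.05 and the 95% interval excluding zero do not coincide.

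| True effect | Bootstrap interval for median difference | Normal-approximation interval for medians | Hodges-Lehmann interval |
|---|---|---|---|
| None | 2.0–2.5% | 3–4% | 0% |
| Ratio 2 | 10–15% | 24–36% | 0% |
| Ratio 3 | 2–18% | 11–29% | 0% |

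For log-normal data with log SD 0.60 and ratio 2, Mann-Whitney was significant in 72.4% of runs. The bootstrap interval contained zero despite significance in 11.5% of runs and excluded zero without significance in 1.2%, so they disagreed in 11.5 + 1.2 = 12.7%, about 1 in 8. As a share of significant results, the first kind was 11.5 / 72.4 = 16%. Over the four shapes at ratio 2 that share ran from 9% to 34%. Where the arms differed in shape as well as location, bootstrap disagreement was 4–11%.

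**3. Why Hodges-Lehmann agrees.** With 12 v 12 the exact two-sided 5% test rejects when U ≤ 37. Sort the 12 × 12 = 144 pairwise differences. The matching interval runs from the 38th to the 107th (37 + 1 and 144 − 37), and it excludes zero exactly when the test rejects. In a separate log-normal check at ratio 2, this interval was also about 12% narrower on the log scale than the bootstrap one.

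**4. How often the branch is reached.** With log-normal data and an assumed 5% Shapiro-Wilk check in each of three arms, about 13% of simulated trials go to Mann-Whitney. Test and interval conflicted within the branch in about 1.5–1.8% of all trials. Within the branch that is 1.5 / 13 = 12% to 1.8 / 13 = 14%. Data that are not log-normal would enter the branch more often.

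**5. Scale.** Raw medians of 100 v 200 and of 500 v 1000 (illustrative) are both twofold, but the differences are 100 and 500. On the log scale both are ln 2 = 0.693, and exp(0.693) = 2.

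**The case against.** The strongest reply is that this is ordinary SAP detail. The interval method, the normality check and any back-transformation are usually fixed there, and a difference in medians printed beside Mann-Whitney is sometimes in fact a Hodges-Lehmann interval. That stands as far as it goes: leaving those details out is no fault of the protocol. But 9.1 does more than leave a gap. It names the test and the effect measure, and taken at their word the two do not belong together.

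Three stronger readings are tempting, and the documents do not support them.

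- *That p-value and interval will often conflict.* Rates near one third need a crude normal-approximation interval, which the protocol does not name. With a bootstrap interval the rate is about 2% under no effect and 10–15% at twofold. Log-normal data mostly go to the t-test instead.
- *That the Mann-Whitney branch reports absolute spot counts.* Section 9.1 does not say so. The data judged non-normal are the log-transformed values, so the medians may well be log medians. The twofold reading is lost only if the raw scale is used. Even then, the ratio of medians can be taken from the planned group summaries; what is missing is an interval for it.
- *That one-week and six-month results will land in different units.* This needs raw medians, a particular normality test and a separate decision at each time point. Section 9.1 states none of these.

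The stakes are also limited. The primary endpoint is safety, and no decision rule in 9.1 depends on the twofold figure.

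**Conclusion.** The point holds in limited form. In the non-normal branch, 9.1 reports a quantity that its test does not assess. Within that branch, test and interval would disagree in about 1 in 8 comparisons at a true twofold effect if a bootstrap interval is used, and in about 2% under no effect. Cruder intervals do worse, and a Hodges-Lehmann interval removes the conflict. The rates assume a log SD near 0.60, the simulated shapes, continuous data without ties and a two-sided 5% level, none of which the protocol gives.

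Separately, the scale of the reported difference is unstated. If it is raw, the interval cannot be set against the ratio that 9.1 calls meaningful.

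The impact is modest, because the endpoints are secondary and the trial is described as primarily descriptive.

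**What to change.** In section 9.1, replace the sentence on differences between means or medians with a rule along these lines:

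- Every between-group effect is reported as a ratio with its 95% confidence interval.
- With the t-test on logs, this is the geometric mean ratio.
- With Mann-Whitney, it is the Hodges-Lehmann shift on log values, back-transformed, with the interval obtained by inverting the same version of the test (including its handling of ties).
- With the Wilcoxon matched-pairs test, it is the signed-rank Hodges-Lehmann estimate, also on log values and back-transformed.
- Medians and interquartile ranges stay as descriptive summaries.

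Both branches then report on one scale that reads directly against twofold, and the Mann-Whitney p-value and interval cannot contradict each other. If an SAP already specifies this, 9.1 need only be brought into line. The cost is a few sentences: no new data, no change in sample size, and standard software.
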